### Inclusion and Exclusion Criteria

The study sample will include approximately 400 adults who smoke cigarettes, between 22 and 65 years of age who have smoked an average of at least 5 commercial brand cigarettes per day for 12 months prior to signing consent. Specific inclusion and exclusion criteria are listed in Textbox 1.

Inclusion and exclusion criteria.
**Inclusion criteria**
Has signed the informed consent form (ICF) and is able to read and understand the information provided in the ICF.Healthy adults who smoke cigarettes and are 22-65 years of age at screening.Smokes an average of at least 5 cigarettes per day for the last 12 months.Does not intend to use a Food and Drug Administration–approved treatment for nicotine dependence within the next 60 days (as assessed at screening).Responds “Yes” to “Are you interested in replacing combustible cigarettes with a smoke-free tobacco product?” when asked at screening.Willing and able to comply with the requirements of the study.Owns a smartphone with SMS text messaging and data capabilities compatible with necessary surveys.
**Exclusion criteria**
Participant enrollment numbers met (in subgroup or entire study).Participant, or their first-degree relative (eg, parent, sibling, child, or spouse) or household member, is a current or former employee of the tobacco or e-vapor industry.Participant, or their first-degree relative (eg, parent, sibling, child, or spouse) or household member, is a named party or class representative in litigation involving a tobacco or e-vapor company.Participant, or their first-degree relative (eg, parent, sibling, child, or spouse) or household member, is a current or former employee of a marketing consultant, market research firm, advertising or promotions agency, TV or radio station, magazine or newspaper, government regulatory agency or public policy advocacy group, or law firm or legal department of a company.Participant self-reports being “in poor health.”Participants of childbearing potential (CBP) who have a positive pregnancy test (as assessed at screening) or are nursing or planning to become pregnant during their participation.Participant has an allergy or sensitivity to menthol or menthol-containing products or phenylalanine.Participant has any other self-reported health restrictions.Participant self-reports cardiovascular disease, cancer, or diabetes or is being treated for high blood pressure.Participant self-reports periodontal disease, gum disease or bleeding, open mouth sores, or ulcers.Participant self-reports as wanting to stop using tobacco products in the next 60 days.Participant has participated in 1 tobacco research study in the past 30 days or a tobacco research study lasting 2 weeks or longer in the past 90 days.Participant is unable to read, speak, or understand English.Participants who ever used at least a pack of nicotine pouch products or currently uses nicotine pouch products.Participant who smokes marijuana more than once a week.Heterosexually active participants of CBP (not sterilized by tubal ligation, oophorectomy, hysterectomy, or other surgical methods, or postmenopausal) who do not agree to practice medically appropriate methods of birth control (or remain abstinent) during the course of the trial and for 30 days after the last use of research product. Medically acceptable methods of birth control include vasectomy, vaginal diaphragm with spermicide, intrauterine device, hormonal birth control (oral, injected, patch, or implanted), condom with spermicide, or sponge with spermicide.Taking psychoactive medications (eg, antipsychotics or mood stabilizers).Cannot participate in the study for any reason (eg, medical, psychiatric, or social reason) as judged by the investigator or designated medical staff based on all available information from the screening period.

### Ethical Considerations

The study protocol and informed consent form (ICF) has been approved by Advarra Institutional Review Board (IRB; Pro00072765). Study conduct will follow the principles set forth by the Belmont Report and, where applicable, guidelines established under 21 Code of Federal Regulations (CFR) § 50 and 56. In addition, study conduct will be in accordance with the ethical principles that have their origin in the Declaration of Helsinki and that are consistent with Good Clinical Practice (GCP) and applicable regulatory requirements. The study must be conducted in accordance with the regulations of the US FDA as described in 21 CFR 50 and 56, applicable laws, and the IRB requirements.

Informed consent will be obtained from all participants remotely through an electronic consent process. Participants will be required to verify that they understand each section of the ICF by checking a box. They will provide their consent at the end of the document by checking a box after reading the consent statement. Electronic copies of the ICF are made available for the participants to download and reference at any time. Participants will be informed that their participation is completely voluntary, and they may discontinue their participation at any time for any reason.

After providing consent, participants will be asked to upload a copy of their government-issued ID for verification. We will use a multistep process for age verification, validation of the uploaded government-issued identification, and to ensure that the person matches the photo on the ID. This process will be conducted by software and research staff. Software will initially determine whether the uploaded ID is valid, verify the individual’s age, and compare previously submitted information against what is detected on the uploaded ID. Any discrepancies at this point will be reviewed by research staff. If the uploaded ID is expired, blurred, or otherwise not valid, the potential participant will be given the opportunity to resubmit and continue the screening process. For those who pass the initial software-level review, research staff will verify that the face on the ID matches the individual who joins the telemedicine session. We rely on human review for this final step for the safety of minors and due to limitations in currently available software.

### Recruitment

Participants will be recruited through IRB-approved, study-specific recruitment advertisements or from the Rose Research Center volunteer database, an Advarra IRB-approved generic volunteer database. Participants will be contacted with IRB-approved materials. These documents will include a brief description of the study and information on how to prescreen for participation. This study will recruit remotely across the United States in North Carolina, Ohio, Georgia, Florida, Michigan, South Carolina, Tennessee, and Pennsylvania. Participant recruitment will be guided by the distribution of demographic characteristics shown in Table 1.

**Table 1 table1:** Demographic distribution of adults who smoke cigarettes based on National Survey on Drug Use and Health (NSDUH) 2021 data.

Demographic subgroup					Prevalence in US adult smoker population, %^a^			Corresponding average expected cell size given (n=400), n
**Sex and age (years)**								
	**Male**			53.9			216	
		21-34	11.0			44		
		35-44	13.2			53		
		45-49	6.1			24		
		50-64	23.6			94		
	**Female**			46.1			184	
		21-34	9.6			38		
		35-44	12.1			48		
		45-49	5.8			23		
		50-64	18.7			75		
**Race or ethnicity**								
	White non-Hispanic			77.7			311	
	Black non-Hispanic			8.1			32	
	Other non-Hispanic			6.3			25	
	Hispanic			7.9			32	
**Education**								
	Less than College			60.4			242	
	Some college			30.20			121	
	College+			9.40			38	
**Menthol preference**								
	Menthol			36.20			145	
	Nonmenthol			63.80			255	

^a^Estimates were based on weighted proportions.

### Study Procedure

This study involves a multistep screening process, a baseline assessment period (3-7 days), 6 weeks of at-home product use, and a 6-month posttrial follow-up survey. During recruitment, participants will sign the ICF, upload a picture of their government-issued ID, complete web-based screening surveys, and download eResearch Advance Science from Home to their smartphones.

All who pass the initial web-based screening will have a CO monitor sent to their home address. At this point, male participants are able to schedule their baseline telehealth session and continue the screening process. Female participants are sent a urine pregnancy test with instructions for completing and uploading results, which are reviewed and confirmed by study staff. Those with confirmed negative pregnancy test results are then able to schedule the baseline telehealth session.

At the baseline telehealth session, participants will be further assessed for eligibility with additional inclusion or exclusion criteria, including a biometrically verified expired-air CO reading. If eligible, they will be randomized to Group I or Group IIa/IIb. During the 3- to 7-day baseline assessment period, participants will provide CO readings every other day and record their cigarette consumption in web-based daily diary survey. Upon the completion of the baseline assessment period, participants will begin week 1 when they receive the research product to use in their natural environment, following group configurations shown in Figure 1. During weeks 1-6, participants will respond to daily diary surveys to report their use of the research product (by flavor, if applicable), cigarette consumption, and use of other tobacco products. They will request and receive research products weekly. They will also be alerted to provide pseudorandom biometrically verified CO readings once every 3 days. At the end of week 3, female participants of childbearing potential will be asked to provide urine pregnancy test results; those with positive results (ie, pregnant) will be discontinued from the study and referred to their primary care provider. Six months after the study ends, participants will be recontacted to complete a follow-up survey with questions related to tobacco-use behaviors (including cigarette smoking and *on!* NP use), reasons to use or not use *on!* NPs, risk perceptions of use of a variety of tobacco products at the category level (eg, cigarettes, smokeless tobacco, and NPs), and respiratory symptoms. The main purpose of the 6-month follow-up survey is to collect information on participants’ posttrial tobacco use behaviors when they are no longer provided with *on!* NPs. None of our research questions rely on the 6-month follow-up survey.

Participants will be presented with the following debriefing statement at the conclusion of the study (ie, at the end of Week 6) or upon discontinuation of participation (ie, withdrawal from the study):

We would like to emphasize that in conducting this research, we were not trying to market, sell or promote a tobacco or nicotine product to you. Finally, oral tobacco-derived nicotine products should never be viewed as an alternative to quitting all tobacco products.

Research will be conducted in the context of participants’ natural environment (ie, home use test). Research products will be shipped to participants weekly.

Participants will receive compensation after successful completion of each study milestone, including the completion of each daily survey, weekly survey, and CO measurement collection throughout the study. An end-of-study bonus will be awarded if the participant completes the entire study.

### Outcome Measures

Primary outcomes of this study are (1) at least 50% reduction in expired-air CO readings from baseline (yes or no) and (2) expired-air CO as a continuous variable (averaged across the week of interest).

Secondary outcomes include (1) at least 50% reduction in self-reported cigarette consumption from baseline (yes or no), (2) CO-verified smoking abstinence (ie, self-reporting no cigarettes smoked in past 7 days and CO<6ppm [22]), and (3) self-reported number of cigarettes smoked (averaged across the week of interest).

Participants who meet the ≥50% cigarette reduction (based on self-reported cigarette consumption) threshold will be identified as “Responders”; those unable to meet this threshold will be identified as “non-Responders.”

We chose to use expired-air CO values in primary outcomes because it is an objective measure not susceptible to recall bias, demand characteristics, or prevarication. Further, expired-air CO closely reflects actual smoke exposure and would not lead to an erroneous conclusion of reduced exposure that results from more intensive smoking of fewer cigarettes as compared to self-reported cigarette consumption. Nonetheless, expired-air CO measures are not without limitation. Factors other than cigarette smoking, such as exposure to environmental pollutants, second-hand smoke, vehicle exhaust, etc, can contribute to elevated expired-air CO, and vigorous exercise can lead to lower expired-air CO. In this study, we include both expired-air CO (taken twice a week) and self-reported cigarette consumption (daily) to provide robust assessments of smoking behavior.

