We hypothesize that access to a complete profile of flavored NP products will result in greater reduction, including greater persistence of reduction, in exposure to a smoking-related toxicant (ie, carbon monoxide [CO]) and cigarette consumption. With objectives 1-3, we intend to assess the hypothesis from 3 different angles (ie, overall effect, maintenance of reduction among responders, and additional reduction among nonresponders). With objective 4, we seek to explore the potential effect of a delayed access to flavored products, which may have regulatory implications for the speed of decision-making on flavored products. We consider objective 4 to be exploratory because it is difficult to simulate such a scenario in a trial context with limited follow-up time.

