Similarly, we will use generalized linear regression with a log link for binary secondary outcomes (ie, at least 50% reduction in cigarette consumption based on self-report and CO-verified smoking abstinence). Generalized estimating equations will be used to analyze cigarette consumption based on the daily diary, with cigarette consumption at baseline as a covariate. Specific comparisons are as follows: (1) for objective 1, comparison will be made between (a) Group I and combined Groups II at Week 3 and (b) Group I and Group IIa at Week 6; (2) for objective 2, comparison will be made between Group IIa and Group IIb at week 6 among nonresponders at week 3; (3) for objective 3, comparison will be made between Group IIa and Group IIb at Week 6 among responders at week 3; and (4) for objective 4, comparison will be made between Group I and Group IIb at week 6.

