#### Power

Sample size calculation was based on the primary outcomes of the study: at least 50% reduction in expired-air CO readings from the baseline numeric CO readings. Because the Original variety is included in the complete flavors, we do not expect the occurrence of the main outcome to be lower in the complete flavor arms compared to the Original arms, so we will use 1-sided tests with an α level of 0.05 and power of 0.80. Sample size calculation was conducted using Stata 16 (StataCorp).

For objective 1, we assumed an incidence of at least 50% reduction in CO readings of 60% in Group I and 45% in the Original arm at week 3, and incidence of the main outcome among 80% in Group I and 60% in Group IIa at week 6. Based on these values, it was estimated that 136 participants and 64 participants per arm will be needed, respectively. Numeric CO readings will be analyzed as a continuous variable, which typically has higher levels of statistical power [26]. Assuming a mean CO of 6 ppm in Group I and SD of 5 [27], a sample size of 136 per arm will be able to detect a difference of 1.7 between study groups.

For objective 2, we assumed an incidence of at least 50% reduction in CO readings for 70% of those in Group IIb and 45% among the Group IIa at week 6 among the nonresponders in Group II (ie, those who did not reduce cigarette consumption by ≥50% at week 3). Based on these values, we estimated that 48 participants per group will be needed. Assuming 55% of participants in Group II will be nonresponders at week 3; we estimated that a total of 175 participants will be needed in Group II at baseline.

For objective 3, we assumed that 85% in Group IIb and 60% in Group IIa will maintain their responder status at week 6 among responders in Group II (ie, those who reduce cigarette consumption by ≥50% at week 3). Based on these values, it was estimated that 39 participants per group will be needed. Assuming 45% of participants in Group II will be responders at week 3, a total of 174 participants will be needed in Group II at baseline.

Based on these calculations, we will randomly assign 150 participants to Group I and 250 participants to Group II at baseline.

Objective 4 is considered exploratory in nature. Given the above sample size, 125 participants per group will be able to detect a difference between 80% and 67% of at least 50% of CO reduction comparing immediate versus delayed access to complete flavor profile.

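### Two primary CO outcomes on four non-exploratory contrasts, each contrast sized at the full one-sided 0.05, and no deciding test: if any of them can carry the flavor claim, its error rate is well above 5%

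*Protocol article*

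**What the plan says.** Under Outcome Measures the article states: "Primary outcomes of this study are (1) at least 50% reduction in expired-air CO readings from baseline (yes or no) and (2) expired-air CO". The second is a numeric value, averaged over the week of interest. The Analytic Plan gives each outcome its own model, a log-link generalized linear model for the binary outcome and baseline-adjusted linear regression for numeric CO. Each is applied at week 3 or week 6 according to the objective and reported with 95% CIs.

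The contrasts in the Analytic Plan are:
- Objective 1 has two: "comparison will be made between (a) Group I and combined Groups II at Week 3 and (b) Group I and Group IIa at Week 6".
- Objective 2 as numbered there: "comparison will be made between Group IIa and Group IIb at week 6 among nonresponders at week 3".
- Objective 3 as numbered there: "comparison will be made between Group IIa and Group IIb at Week 6 among responders at week 3".
- Objective 4: Group I v IIb at week 6. The Power section sets it apart: "Objective 4 is considered exploratory in nature".

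The Introduction ties the first three objectives together: "With objectives 1-3, we intend to assess the hypothesis from 3 different angles (ie, overall effect, maintenance of reduction among responders, and additional reduction among" (the list ends with nonresponders). The Power section sets the level, "so we will use 1-sided tests with an α level of 0.05 and power of 0.80", and then sizes each contrast separately.

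The Analytic Plan assigns nonresponders to objective 2 and responders to objective 3. The objectives listed in the Introduction have these the other way round. The number of tests is the same either way, so contrasts are named below by population.

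**The concern.** Two outcomes on four contrasts make eight tests of what the Introduction presents as one hypothesis. The document gives no order, no alpha split and no rule that all must succeed. Read as written, any one of eight results could be presented as primary evidence that flavors increase smoking reduction.

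The plan also leaves conflicting results unsettled, for example numeric CO positive with the binary outcome null, or week 3 positive with week 6 null. This matters because the trial is open-label, tests in one direction only, and is described in the Discussion as direct evidence on what a flavor ban would cost.

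**Working it through.** **1. Is each contrast sized at the full alpha?** For two proportions with pooled variance and no continuity correction, with p̄ = (p1 + p2)/2:

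n = [z(1−α)·√(2p̄(1−p̄)) + z(0.80)·√(p1(1−p1) + p2(1−p2))]² / (p1 − p2)²

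The rates come from the Power section; z(0.95) = 1.645 and z(0.80) = 0.842.

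| Contrast | Rates | One-sided 0.05 | Stated | Two-sided 0.05 |
|---|---|---|---|---|
| I v II, week 3 | 60% v 45% | 136.0 → 136 | 136 | 173 |
| I v IIa, week 6 | 80% v 60% | 63.9 → 64 | 64 | 82 |
| IIb v IIa, nonresponders | 70% v 45% | 47.3 → 48 | 48 | 61 |
| IIb v IIa, responders | 85% v 60% | 38.4 → 39 | 39 | 49 |

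All four stated sizes reproduce at an undivided one-sided 0.05. The numeric CO figure does not follow the same rule. With SD 5 and 136 per arm, the detectable difference is 1.51 one-sided and 1.70 two-sided, and the article states 1.7. The level for numeric CO is therefore not settled by the text.

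**2. Error rate if the tests were independent.** 1 − (1 − α)^k:
- k = 8, α = 0.05: 1 − 0.95⁸ = 33.7%
- k = 6, α = 0.05: 1 − 0.95⁶ = 26.5%
- k = 4, α = 0.05: 1 − 0.95⁴ = 18.5%
- k = 8, α = 0.025: 1 − 0.975⁸ = 18.3%

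**3. Error rate with correlation.** The document gives no correlations, so these are assumed. Trials of 150/125/125 were simulated with no flavor effect. Assumptions: log-normal baseline CO, log-change SD 0.6, 45% responders at week 3, and week 3-week 6 correlation 0.3 to 0.9. The binary outcome was tested by a pooled z test and numeric CO by regression on arm and baseline. The two outcomes' test statistics then correlate at about 0.6-0.7.

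| Reading | Chance of at least one false positive |
|---|---|
| 8 tests, one-sided 0.05 | 25-27% |
| 6 tests (no CO tests in week-3 responders) | 19-21% |
| Binary outcome only, 4 contrasts | 16-18% |
| Objective 1 only, 4 tests | 12-15% |
| 8 tests, one-sided 0.025 (95% CI reading) | 13-15% |

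A multivariate-normal model of the eight statistics, with contrast correlations taken from the allocation, gives 16-31% at one-sided 0.05 as the outcome correlation runs over its whole range from 0 to 1.

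**4. Power under a fixed sequence.** Planned sizes are 150 v 125, 150 v 250, 69 v 69 (125 × 0.55 = 68.75) and 56 v 56 (125 × 0.45 = 56.25). A step counts only if all earlier ones succeed, so step powers are multiplied, treating steps as near-independent.

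| Step | Alone, 0.05 | Cumulative | Alone, 0.025 | Cumulative |
|---|---|---|---|---|
| 1. I v IIa, week 6 | 0.977 | 0.98 | 0.954 | 0.95 |
| 2. I v II, week 3 | 0.899 | 0.88 | 0.831 | 0.79 |
| 3. Nonresponders | 0.915 | 0.80 | 0.852 | 0.68 |
| 4. Responders | 0.915 | 0.74 | 0.852 | 0.58 |

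Positive correlation between steps would raise the cumulative figures somewhat. Step 4 uses 85% v 60%, which the Power section gives for maintaining responder status. The plan states no CO-reduction rates for responders.

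**The case against.** The strongest reply is that testing order and alpha allocation usually sit in the SAP, which is not shown, and that a fixed sequence would also size each step at full alpha. This stands as a limit: a reader might infer that the trial has no multiplicity rule at all, and the article cannot show that. The point still holds for what the article itself fixes, namely two primary outcomes, two time points for objective 1, and one hypothesis approached through several full-alpha contrasts.

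Other objections also carry weight:
- The Power section calls the binary reduction the main outcome and sizes every contrast except the responder one on it. That leans toward the binary outcome but is not a decision rule, and four binary contrasts still give 16-18%.
- One-sided 0.05 appears only under Power, while the Analytic Plan reports 95% CIs. On that reading the figure for 8 tests is 13-15%.
- Objective 3 is powered on responder status, which Outcome Measures defines by self-reported cigarettes. Without its CO tests there are six tests, not eight.
- Whether separate objectives form one family is debated. The Introduction's description of one hypothesis seen from several angles favors treating them together.

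A reader might also infer that the secondary outcomes are tested at full alpha. The document states no alpha for them, so that is not supported.

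**Conclusion.** The concern holds as a range rather than a single figure. If any of the primary CO results on the four non-exploratory contrasts can support the flavor claim, the family-wise one-sided error is well above the stated 0.05. The main estimate is 25-27% for 8 tests, and narrower readings of the test count or the level bring it to about 20%, 16-18% or 13-15%. All of these assume no flavor effect on any contrast and rest on correlations the document does not give. The structural facts and the full-alpha sizing need no such assumption.

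Two stronger readings should be avoided. One is that 26% is the trial's error rate, since it is one value within a range. The other is that a fixed sequence keeps every planned power, since the figures above 90% for the last two steps are for each step taken alone.

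**What to change.** Before the data are analysed, in the protocol and SAP:
1. Name one deciding outcome and contrast, for example at least 50% CO reduction, Group I v IIa at week 6, and state that the trial's confirmatory claim rests on it.
2. Test the other contrasts in a fixed order at full alpha, each only if all earlier ones succeed. One possible order is Group I v combined II at week 3, then IIa v IIb at week 6 in week-3 nonresponders, then in week-3 responders. Name populations rather than objective numbers, and reconcile the numbering of objectives 2 and 3.
3. Treat numeric CO as supportive, or place it last in the sequence.
4. State that the secondary outcomes and objective 4 carry no confirmatory claim.
5. State once whether the level is one-sided 0.05 or 0.025, to agree with the 95% CIs.

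The cost is wording, with no added participants. The deciding test keeps about 98% power (95% at 0.025). A contrast after a failed step can no longer be claimed as confirmatory. In the example order the last step falls to about 74%, below the planned 80%; at 0.025 steps 2 to 4 fall to about 79%, 68% and 58%. The sponsor may prefer an order that puts the contrast it values most earlier, and should state the CO-reduction rates it expects in responders.

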### Analytic Plan

A description of recruitment will be reported, including the number of participants who are recruited, pass screening, are randomized, complete weeks 1-3, enter week 4, complete the trial (ie, weeks 1-6), and complete the 6-month follow-up.

We will use descriptive statistics to characterize the distribution of demographic variables, tobacco use history (ie, cigarettes per day, use of other tobacco products, and menthol cigarette preference), and CO at baseline. We will examine the aforementioned demographic variables and tobacco use history variables among responders and nonresponders for potential imbalance. If such imbalance is discovered, respective variables will be adjusted in the analysis as covariates.

The analysis will be conducted on an intention-to-treat basis. Primary outcome variables include a binary (yes or no) variable indicating at least 50% reduction in CO readings from baseline and a numeric variable for expired-air CO. For individuals who drop out of the study prematurely, they will be assumed not achieving at least 50% reduction in CO readings, and their numeric CO reading variable after those last reported will be replaced with their baseline CO readings.

To compare incidence proportions of at least 50% reduction in CO readings between study groups at each time point (week 3 or week 6, depending on the objective), generalized linear regression models with a log link will be used to generate incidence ratios and their 95% CIs. To compare numeric CO readings between study groups at each time point (week 3 or week 6, depending on the objective), linear regression will be used to compare group-level differences in CO readings and their 95% CIs when adjusting for baseline CO reading. We chose to use linear regression adjusting for baseline CO reading over ANOVA for change in CO readings from baseline because the adjustment approach properly corrects for “regression to the mean,” provides greater statistical power, and produces unbiased estimates [23-25].

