### Limitations

One potential study limitation is that blinding is not feasible. Consequently, participants are aware of their group assignment. We use expired-air CO as our primary outcome to minimize potential biases in participants’ self-reported cigarette consumption. Another possible limitation is the relatively short study duration (ie, a total of 6 weeks). This study design aspect was a result of balancing feasibility and available resources while also providing sufficient time for participants to achieve a meaningful reduction in their cigarette consumption. Due to the relatively short study duration, we chose at least a 50% reduction in CO values as one of our primary outcomes—and abstinence as one of our secondary outcomes—considering we may not be able to observe the full course of smoking cessation. Previous studies using the same research products have shown measurable changes in smoking behavior in a similar timeframe [13]. Finally, this study uses a nonprobability sample, a common challenge of clinical trials. We try to mitigate these limitations by setting population quotas to align the sample with the adults who smoke cigarettes population in key demographic characteristics.

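### Two co-equal CO primary outcomes have no stated success rule: if either can win, the false-positive rate per contrast is about 8% instead of 5%; the objective 4 power figure is also overstated

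*Protocol article*

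**What the plan says.** Outcome Measures in the protocol article lists two primary outcomes side by side: "Primary outcomes of this study are (1) at least 50% reduction in expired-air CO readings from baseline (yes or no) and (2) expired-air CO" averaged over the week of interest. The Analytic Plan repeats the pair: "Primary outcome variables include a binary (yes or no) variable indicating at least 50% reduction in CO readings from baseline and a numeric variable". It gives each its own model: a log-link regression for the binary outcome, and a linear regression adjusted for baseline CO for the numeric one. Neither section ranks them, divides the error rate, or says whether success needs one or both.

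The Power section sets the test: "so we will use 1-sided tests with an α level of 0.05 and power of 0.80". Its required sizes come from proportions: "Sample size calculation was based on the primary outcomes of the study: at least 50% reduction in expired-air CO readings". Numeric CO receives one detectable difference, for objective 1, with the remark "Numeric CO readings will be analyzed as a continuous variable, which typically has higher levels of statistical power". For exploratory objective 4 the section says "125 participants per group will be able to detect a difference between 80% and 67% of at least 50% of CO reduction".

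The Limitations section explains the choice of a 50% reduction by the short study, with abstinence placed among the secondary outcomes: "we chose at least a 50% reduction in CO values as one of our primary outcomes". It does not say how that outcome relates to the other primary outcome.

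**The concern.** The binary outcome is the CO reading cut at half of baseline, and the numeric outcome is the same reading uncut. Each contrast therefore gets two correlated chances at a positive primary result, each at the full one-sided 0.05. If either may carry the claim, the error rate per contrast exceeds the stated 5%. If both are required, the error rate is safe, but the power statement, made for one outcome at a time, no longer describes the chance of success. The two outcomes can also disagree, and the plan gives no basis for saying which one answers the objective.

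**Working it through.** **Inputs from the Power section.** One-sided alpha 0.05, power 0.80. Objective 1: 60% v 45% at week 3, 80% v 60% at week 6. Nonresponders: 70% v 45%. Responders: 85% v 60%. Objective 4: 80% v 67%, 125 per group. Allocation is 150 in Group I and 250 in Group II (125 + 125).

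**1. Reproducing the plan's sizes.** With p̄ the mean of the two proportions,

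n = [z_α √(2p̄(1−p̄)) + z_β √(p1(1−p1)+p2(1−p2))]² / (p1−p2)²,

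with z_α = 1.645 and z_β = 0.842. This gives 136, 64, 48 and 39 per arm, exactly as stated. So the binary outcome was sized at the full one-sided 0.05, with nothing reserved for the second primary outcome.

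**2. Error rate if either outcome can win.** Under the null the two test statistics are taken as bivariate normal with correlation ρ:

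P(at least one false positive) = 1 − Φ₂(1.645, 1.645; ρ).

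| ρ | Rate |
|---|---|
| 0 | 1 − 0.95² = 9.75% |
| 0.5 | 8.8% |
| 0.7 | 8.0% |
| 0.8 | 7.5% |
| 0.9 | 6.8% |

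The documents do not give ρ, so it is an assumption. A null simulation of 150 v 250 with lognormal CO, the binary test and the baseline-adjusted regression gave ρ of 0.54 to 0.64 and rates of 7.9% to 8.4%.

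**3. If both must succeed.** The error rate stays at or below 5%. Power cannot exceed the lower of the two. For two outcomes with 80% power each, it lies between 0.80 + 0.80 − 1 = 60% and 80%.

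**4. Does an equal split fit the planned sizes?** The same formula at one-sided 0.025 for the binary outcome, before dropout, with strata of 125 × 0.55 ≈ 69 and 125 × 0.45 ≈ 56 per group:

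| Contrast | Needed per arm | Planned | Power at 0.05 | Power at 0.025 |
|---|---|---|---|---|
| Objective 1, week 3 | 173 | 150 v 250 | 90% | 83% |
| Objective 1, week 6 | 82 | 150 v 125 | 98% | 95% |
| Nonresponders (objective 2 in Power) | 61 | about 69 | 91% | 85% |
| Responders (objective 3 in Power) | 49 | about 56 | 92% | 85% |

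The responder row uses the plan's 85% v 60%. That is the share keeping responder status, which Outcome Measures defines by self-reported cigarettes, so it is not strictly a figure for the CO outcome.

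**5. Objective 4.** On the test that reproduces the four sizes, with 125 per group and p̄ = 0.735:

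- Standard error under the null: √(2 × 0.735 × 0.265 / 125) = 0.0558.
- Under the alternative: √((0.80 × 0.20 + 0.67 × 0.33)/125) = 0.0552.
- Power = Φ[(0.13 − 1.645 × 0.0558)/0.0552] = Φ(0.69) = 75.5%.

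For 80% power, 80% v 67% needs 142 per group; 80% v 66% needs 124. With the actual 150 v 125, power for 80% v 67% is 78.9%.

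**The case against.** The strongest reply is that this is a condensed article and that a rule linking two primary outcomes is often placed in the statistical analysis plan, which is not shown. That stands in part: the rule may exist. But the article itself fixes the two primary outcomes, the models, the alpha and the sidedness, and it sizes the binary outcome with the whole 0.05. A split added later would change the design as sized, and an order would change what each outcome can claim.

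A second reply also stands. The inflation exists only if either outcome can win, and the article never says so.

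A third is that the 50% reduction is not arbitrary. It frames the responder objectives, appears in both earlier studies the protocol describes, and is easy to interpret beside the continuous measure. Agreed: nothing here calls for removing it.

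A reader might go further and infer that the trial rests on the weaker scale, so that putting numeric CO first would gain power. The documents do not support that. Numeric CO is itself primary, with its own analysis; only the sizing uses the cut. The plan's remark that numeric outcomes typically have more power is general. Translating 60% v 45% into a shift of 0.379 SD on a latent normal scale does favour the uncut measure (87 v 136 per arm), but the planned analysis is of raw ppm. Simulations of that analysis, with the cut held at 60% v 45%, 150 v 250, no dropout and an assumed lognormal baseline, gave numeric power of 91%, 84% and about 79% for log-ratio SDs of 0.5, 0.8 and 1.0. With a mixture of reducers and non-reducers it was about 68%. The cut had about 89% to 90% throughout. The ranking can reverse.

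On objective 4, the plan labels it exploratory, and with the actual group sizes the shortfall is about one point. The sentence as written is still wrong for 125 per group.

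**Conclusion.** The point holds in a limited form. Two co-equal primary outcomes from the same readings are each given the full one-sided 0.05, with no rule linking them. If either may win, the error rate is about 8% per contrast (6.8% to 8.8% for ρ from 0.9 to 0.5, and at most 9.75% unless the tests are negatively correlated). If both are required, there is no inflation but power is below that of either alone.

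The 8% should not be read as the trial's overall rate. It is for one contrast; objective 1 alone has two time points, hence four tests, and about 12% to 16% under assumed correlations of 0.55 to 0.8 between outcomes and 0.3 to 0.7 between times. Nor do the documents settle which outcome should lead.

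The objective 4 error is exact and small: 75.5% power where 80% is implied.

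**What to change.** In Outcome Measures and the Analytic Plan, state one rule for each contrast. Either:

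- **Fixed sequence:** name the lead outcome in advance, test it at one-sided 0.05, and test the other at 0.05 only if the first succeeds. Cost: the second outcome loses its formal claim when the first fails. The choice of lead should be argued, not assumed from the general remark on power.
- **Split:** test each at one-sided 0.025. Cost: for the binary outcome, about 7 points of power at week 3 and 3 to 6 or 7 points elsewhere, leaving 83% to 95% before dropout. Dropouts count as failures, so dropout would lower these figures.

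Either rule holds 5% within a contrast only. In the Power section, give power under the chosen rule and correct objective 4: state about 80% v 66% for 80% power with 125 per group, or keep 80% v 67% and state 75.5% (78.9% with 150 v 125). All of this is wording; no new data or participants are needed.
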